### **Primary Endpoint Analysis**

Descriptive analysis will be provided for the primary endpoint Adjudicated Composite rate of all Death, all Myocardial Infarction (MI) and Target Vessel Revascularization (TVR) at 1 year. Counts, percentages and exact 95% confidence intervals will be calculated.

The primary endpoint will be evaluated on the SPIRIT WOMEN Single Arm Study intent-to-treat population, on the randomized sub-study intent-to-treat population and on the Single Arm Study intent-to-treat population pooled with the patients from the intent-to-treat population in the randomized sub-study who were randomized to XIENCE EECS.

### **Randomized Sub-study – Analysis of In-stent Late Loss at 270 days**

Statistical testing of the in-stent Late Loss endpoint will be one-tailed and performed at the 0.05 significance level for the comparison of XIENCE arm to CYPHER arm. The hypothesis testing will be based on all target lesions in the intent-to-treat population. The null hypothesis will be evaluated using a

non-inferiority test with asymptotic test statistic. If the correlation between lesions within patients is large, then repeated measures analysis will be considered.

If non-inferiority is shown and the in-stent Late Loss is lower in the XIENCE arm, then superiority analysis might be performed using a two-sided t-test at the 5% level.

In case the use of parametric tests is inappropriate due to the distribution assumptions violation, non-parametric tests will be considered.

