#### **4.3 Measures to be taken to Avoid/Minimize Bias**

A centralized randomization/registration service will be used. Randomization/registration should be done only after confirmation of angiographic inclusion criteria and before implantation of the first stent. Once randomized/registered the patient is considered enrolled in the study.

A subset of approximately 450 patients will be randomized in a 2:1 ratio in the randomized sub-study. Randomization will be stratified by diabetes mellitus (diabetic vs. non-diabetic), and lesion characteristics (complex vs. non-complex). Complex lesion characteristics include triple vessel treatment, or dual lesion per vessel treatment, or lesions involving RCA-aorto-ostial locations, or bifurcations lesions in which the side branch is  $\geq 2$  mm in diameter, or bifurcation lesions in which the ostium of the side branch is  $> 50\%$  stenosed. For patients enrolled in the randomized sub-study, once randomization is completed and a treatment is assigned, crossover is not permitted.

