### **Randomized Sub-study:**

The overall sample size for the randomized sub-study is based on the main secondary endpoint of in-stent Late Loss at 270 days.

The sample size calculation is based on the following assumptions:

One-tailed non-inferiority test

$\alpha = 0.05$

Power = 90 %

Randomization ratio is 2 (XIENCE EECSS arm) : 1 (CYPHER arm)

True mean in-stent Late Loss is assumed to be equal for both treatment arms

Standard deviation is assumed to be 0.53 mm in both XIENCE EECSS arm and CYPHER arm

Non-inferiority margin delta ( $\delta$ ) of 0.17 mm

Given the above assumptions, approximately 252 subjects in the XIENCE EECSS arm and 126 subjects in the CYPHER arm will be required. In order to account for dropouts and to ensure enough angiographic data, approximately 450 subjects will be enrolled, of which approximately 300 will be in the XIENCE EECSS arm and approximately 150 in the CYPHER arm.

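### The late-loss non-inferiority analysis names neither randomisation stratum; adjusting for both would be a small, free gain in precision

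*Protocol*

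**What the plan says.** Section 4.3 of the protocol fixes the allocation scheme: "Randomization will be stratified by diabetes mellitus (diabetic vs. non-diabetic), and lesion characteristics (complex vs. non-complex"). Complexity covers, among other features, treatment of three vessels or of two lesions in one vessel.

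Section 9.2 sizes the sub-study on in-stent late loss. It assumes a one-sided 0.05 test, 90% power, an SD of 0.53 mm in both arms, equal true means, a margin of 0.17 mm and 2:1 allocation, and arrives at 252 + 126 evaluable patients. The strata do not enter.

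Section 9.4 describes the late-loss analysis in some detail. The test "will be one-tailed and performed at the 0.05 significance level". On the unit of analysis: "The hypothesis testing will be based on all target lesions in the intent-to-treat population". The method is a "non-inferiority test with asymptotic test statistic". Clustering is handled conditionally: "If the correlation between lesions within patients is large, then repeated measures analysis will be considered". If non-inferiority is met and late loss is lower with XIENCE, "then superiority analysis might be performed using a two-sided t-test at the 5% level". Non-parametric tests are a further fallback. Diabetes and lesion complexity are not mentioned. The same section makes this non-inferiority test the criterion for success of the sub-study.

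The protocol expressly leaves to the statistical analysis plan only the female-demographic analyses (section 5.2) and further subgroup analyses (section 9.4). The SAP was not available for this check.

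**The concern.** Stratified allocation nearly balances the arms on both factors, so variation in late loss between strata drops out of the true variance of the arm difference. An unadjusted two-sample standard error still contains that variation. If the factors predict late loss, the estimated standard error is too large and the bound compared with 0.17 mm is too wide.

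Two features of this design add to the reason for naming the strata.

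- The analysis counts lesions, and complex patients will tend to contribute more of them, so balance by patient does not ensure balance by lesion.
- Missing data are excluded (section 9.6), and only patients who received a study stent have follow-up angiography (section 8.2), so randomised balance need not survive into the analysed set.

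At stake is some precision on the test that decides the sub-study, and whether the adjusted or the unadjusted result is fixed as primary in advance.

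**Working it through.** **Inputs.** From section 9.2: margin 0.17 mm, SD 0.53 mm, true difference 0, one-sided level 0.05, power 90%, 252 + 126 evaluable patients. R², the share of late-loss variance explained by the two strata, is not in the protocol. It is an assumption, varied here from 0 to 0.20. One lesion per patient is assumed throughout.

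**The plan's own figure.** With 2:1 allocation and the normal approximation, the control-arm size is 1.5 × (0.53/0.17)² × (1.645 + 1.282)² ≈ 125, giving 125 + 250. The noncentral t version gives exactly 126 + 252, with 90.1% power. The stated sample size therefore reproduces from an unadjusted two-sample calculation and needs no correction.

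**Standard error.** Unadjusted SE = 0.53 × √(1/252 + 1/126) = 0.0578 mm, so 0.17/SE = 2.94. Adjusted SE = 0.0578 × √(1 − R²), which is also the true SE of the unadjusted difference after stratified allocation.

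**Level and power.** Φ is the standard normal distribution function.

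- True level of the unadjusted test: 1 − Φ(1.645/√(1 − R²))
- Power of the unadjusted test: Φ((2.94 − 1.645)/√(1 − R²))
- Power of the adjusted test: Φ(2.94/√(1 − R²) − 1.645)

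| Assumed R² | SE overstated by | True one-sided level, unadjusted | Power, unadjusted | Power, adjusted |
|---|---|---|---|---|
| 0 | 0% | 5.00% | 90.2% | 90.2% |
| 0.02 | 1.0% | 4.83% | 90.5% | 90.7% |
| 0.05 | 2.6% | 4.57% | 90.8% | 91.5% |
| 0.10 | 5.4% | 4.15% | 91.4% | 92.7% |
| 0.20 | 11.8% | 3.30% | 92.6% | 95.0% |

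**Width of the bound.** The one-sided half-width is 1.645 × 0.0578 = 0.095 mm unadjusted. Adjustment shortens it by about 0.002 mm at R² = 0.05 and 0.005 mm at R² = 0.10.

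**In patients.** For 90% power, the ratio of unadjusted to adjusted sample size is [(1.645 + 1.282√(1 − R²)) / ((1.645 + 1.282)√(1 − R²))]². This is 1.029 at R² = 0.05 and 1.062 at R² = 0.10. Then 0.029 × 378 ≈ 11 patients and 0.062 × 378 ≈ 23 patients.

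**Simulation check.** The set-up was 378 patients, permuted blocks of 6 in four strata, an assumed 30% prevalence of each factor, and 10,000 runs per setting. At R² = 0.05 and 0.10 the unadjusted level was 4.4% and 4.0%, and the adjusted level 4.9% and 4.8%. Power was 90.5% against 91.2%, and 91.4% against 92.6%. This agrees with the formulas.

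**A rough guide to R².** Section 2.1.1 reports in-stent late loss with the sirolimus stent of 0.19 mm in a diabetic-only trial, against 0.09 mm and 0.13 mm in two broader trials. With an assumed 30% diabetic share, a gap of 0.06 to 0.10 mm gives a between-stratum variance of 0.21 × gap². Divided by 0.53², that is an R² of about 0.3% to 0.7%. Divided by the square of the 0.27 mm SD reported for XIENCE V in SPIRIT II, it is 1.0% to 2.9%. These are cross-trial comparisons and leave out complexity, but they do not suggest a large R² from diabetes alone.

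**The case against.** The strongest objection is that the protocol is silent here and has not chosen an unadjusted analysis. A Wald statistic from a model with arm and strata is also an asymptotic test statistic. The t-test is optional and does not decide success. Model covariates are often set in the SAP, which may already contain them.

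Much of this stands. A reader might infer that the protocol excludes the strata; it does not say so. Against that, section 9.4 goes as far as the unit of analysis, the population, the sidedness and the fallbacks. It also names a plain t-test, the sample size rests on an unadjusted calculation, and section 9.7 requires a protocol amendment for major changes to the statistical plan. A request to state the adjustment in section 9.4 is therefore reasonable.

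The second objection is that the error is harmless in direction. It stands in full: an oversized standard error cannot make false non-inferiority more likely, and the sample size already allows for an unadjusted SD.

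The third is that the levels in the table are not those of the planned test, which counts all target lesions. That also stands. Uncorrected correlation between lesions of one patient tends to make the standard error too small, so the net direction for the lesion-level test is not established.

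**Conclusion.** The point holds as a free improvement of minor weight. Randomisation uses two factors that the deciding analysis does not name, and adjusting for them is better practice at no cost. The gain is about 0.7 points of power at R² = 0.05 and 1.3 points at R² = 0.10, equivalent to about 3% and 6% of patients. It is nil at R² = 0. These figures rest on an assumed R² and on one lesion per patient.

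Three stronger readings are tempting, and the protocol does not support them.

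- That the test is invalid: taken alone, leaving out the strata makes it conservative, and power stays at or above the planned 90%.
- That adjustment lifts power from 90.2% to 91.5% or 92.7%: the 90.2% baseline ignores the benefit that stratified allocation already gives the unadjusted difference, and using it roughly doubles the apparent gain.
- That the factors were chosen because they predict late loss: section 4.3 lists them under measures against bias and says nothing about their prognostic strength.

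**What to change.** Add to the late-loss paragraph of section 9.4 that the arm difference, its one-sided confidence bound for non-inferiority and any superiority test come from a linear mixed model. The model has fixed effects for arm, diabetes and lesion complexity as recorded at randomisation, and a patient-level random effect for lesions within patients. Report the unadjusted difference as supportive. Fitting the patient effect from the start also replaces the rule that repeated measures are considered only if the correlation proves large, so one model settles both sources of error in the standard error. If the SAP already says this, a cross-reference is enough.

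The cost is one or two sentences. The stratum values are collected at randomisation, and neither the sample size nor the conduct of the study changes.

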#### 6.4.2 Angiographic Inclusion Criteria

- Patients' artery morphology and disease is suitable to be optimally treated with a maximum of 4 planned study stents.

- Target lesions must be de novo lesions (no prior stent implant, no prior brachytherapy).
- Target vessel reference diameter must be between 2.5 mm and 4.0 mm by visual estimate. The diameter range will be expanded to 2.25 mm when the 2.25 mm stent is available.
- Target lesion  $\leq$  28 mm in length by visual estimate.

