**Reference Vessel Diameter (RVD)**

An approximation of the diameter of the vessel at the location of the target lesion. RVD is visually estimated during angiography by the Investigator and it is measured during QCA by the Angiographic Core Laboratory

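### The late-loss non-inferiority test is valid and adequately powered, but it names no baseline covariate although vessel diameter and lesion length are assessed before randomisation: a small precision gain is missed

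*Protocol*

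**What the plan says.** Section 9.4 of the protocol specifies a "non-inferiority test with asymptotic test statistic" on all target lesions of the intent-to-treat population. The test "will be one-tailed and performed at the 0.05 significance level for the comparison of XIENCE arm to CYPHER arm". Repeated measures analysis is held in reserve for strong correlation between lesions of one patient, a two-sided t-test for a later superiority claim, and non-parametric tests if distributional assumptions fail. None of these mentions a baseline covariate. The same section rests the success of the sub-study on this test.

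The sample size in 9.2 is set on the unadjusted scale: "Standard deviation is assumed to be 0.53 mm in both XIENCE EECSS arm and CYPHER arm".

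On the available measurements:
- Section 7.2 has reference diameter and lesion length checked by eye on the pre-procedure angiogram. Patients are randomised only after that check.
- Section 7.3.3.2 puts sub-study baseline angiography under core-laboratory guidelines.
- Appendix II says of reference vessel diameter (RVD): "RVD is visually estimated during angiography by the Investigator and it is measured during QCA by the Angiographic Core Laboratory".
- Section 6.4.2 admits vessels of 2.5 to 4.0 mm and lesions up to 28 mm, and adds: "The diameter range will be expanded to 2.25 mm when the 2.25 mm stent is available".

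Section 4.3 stratifies randomisation by diabetes and by lesion complexity. Complexity is built from triple-vessel treatment, two lesions treated in one vessel, RCA aorto-ostial site and certain bifurcations. Vessel diameter and lesion length are not part of it.

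**The concern.** If vessel diameter and lesion length predict late loss, an analysis that ignores them leaves their variance in the error term. Any chance difference between the arms in these measurements also stays in the estimated treatment difference. The stratification does not balance them directly, and the eligible diameter range may widen during recruitment. The control arm is small, at about 126 evaluable patients, and one mean difference decides the sub-study. A linear model with baseline covariates would recover that precision while estimating the same mean difference against the same margin.

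**Working it through.** **Inputs from section 9.2 and section 9.4.** "One-tailed non-inferiority test"; α = 0.05; power 90%; allocation 2:1; standard deviation (SD) 0.53 mm; margin 0.17 mm; 252 and 126 evaluable patients; 450 enrolled (300 and 150). On the true difference: "True mean in-stent Late Loss is assumed to be equal for both treatment arms".

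**Assumed input.** R², the share of late-loss variance explained by the covariates. The protocol gives no value, so 2%, 5% and 10% are used.

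**Step 1: reproduce the plan's figure.** Normal approximation for the control arm:

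n = (1 + 1/2) × (1.645 + 1.282)² × 0.53² / 0.17² ≈ 124.9, so 125.

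That gives 125 + 250 = 375. With the noncentral t distribution, power is 89.9% at 125/250 and 90.1% at 126/252, which yields the stated 126 + 252 = 378. The plan's sample size is correct for an unadjusted test.

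**Step 2: unadjusted precision at 252/126.**

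SE = 0.53 × √(1/252 + 1/126) = 0.0578 mm.

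Power = Φ(0.17/0.0578 − 1.645) = Φ(1.295) = 90.2%.

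Non-inferiority is shown if the observed difference is below 0.17 − 1.645 × 0.0578 = 0.075 mm.

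**Step 3: with adjustment.** The SE is multiplied by √(1 − R²). The chance shift that adjustment removes has an SD of 0.0578 × √R².

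| Assumed R² | SE (mm) | Power at 252/126 | Evaluable N for 90% power | SD of chance shift removed (mm) |
|---|---|---|---|---|
| 0 | 0.0578 | 90.2% | 375 | 0 |
| 2% | 0.0572 | 90.7% | 369 | 0.008 |
| 5% | 0.0564 | 91.5% | 357 | 0.013 |
| 10% | 0.0549 | 92.7% | 339 | 0.018 |

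Expressed as additional evaluable patients, 378/(1 − R²) − 378 gives about 8, 20 and 42. The chance shift is about 5% (0.008/0.17) to 11% (0.018/0.17) of the margin.

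**Step 4: limits of the calculation.** These figures follow section 9.2 and count patients, as if each had one lesion. The test itself is on lesions. With several lesions per patient, both the adjusted and the unadjusted SE depend on the within-patient correlation, which the protocol does not give.

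**The case against.** The strongest reply is that nothing here is wrong. Randomisation makes the unadjusted comparison valid. Chance imbalance is already part of the 0.0578 mm standard error, so both α and power hold without adjustment. Section 9.2 also enrols 450 against 378 needed; if all 450 were evaluable, unadjusted power would be 94.1%. All of this stands.

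A second reply is that the wording in 9.4 does not exclude a model-based statistic and that covariates are often fixed in the SAP, which is not at hand. This stands in part. The protocol sends other analyses to the SAP explicitly (female demographics in 5.2, subgroups in 9.4) but not this test. Its fallbacks and its sample size also read as comparisons of raw means.

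Three stronger readings are tempting, and the protocol supports none of them:
- A reader might infer that all protection against imbalance is given up. Section 4.3 stratifies by diabetes and complexity, which gives some. A nearer gap is that 9.4 does not carry those two factors into the test.
- A reader might infer that the change in the lower diameter limit biases the comparison. It applies to both arms whenever it takes effect, so it does not.
- A reader might infer that core-laboratory values of both measurements exist for every target lesion. Section 7.3.2 does not list the parameters entered in the eCRF. Quantitative angiography (QCA) is stated for RVD but nowhere for lesion length, which appears only as a visual estimate.

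A plain linear model would also be a poor replacement. The test is on lesions, so ignoring clustering within patients could understate the standard error and offset the small gain.

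**Conclusion.** The point holds as an optional improvement of low severity. The late-loss test is valid, and its sample size reproduces. The protocol nevertheless names no baseline covariate for the analysis that decides the sub-study, while two plausible ones are assessed before allocation and are not balanced by design.

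For an assumed R² of 2% to 10%, the gain is 0.5 to 2.5 percentage points of power, and the chance shift removed is small against the margin. It could matter only for a result close to the 0.075 mm threshold. Two assumptions carry this: the R² range, which has no source in the protocol, and the patient-level calculation. A reader might conclude that the planned test is biased or underpowered; the reproduced figures show neither.

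**What to change.** State in 9.4 that the treatment difference and its one-sided 95% limit come from a lesion-level linear model of in-stent late loss that:
- accounts for clustering of lesions within patients;
- includes the stratification factors, diabetes and lesion complexity;
- includes pre-procedure RVD by core-laboratory QCA and lesion length by the investigator's visual estimate, the only source the protocol states for length.

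Use one measurement source per covariate, without substituting visual for QCA values. Use no post-procedure values: post-procedure minimum lumen diameter arises after randomisation and is part of the endpoint. Keep the margin and hypothesis, and report the unadjusted difference as supportive. If the test is meant to be unadjusted, say so.

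The cost is a few sentences and no added patients or visits. Two checks come first: that the eCRF holds lesion length for each target lesion, and that the core laboratory reads RVD on the pre-procedure film. Because this test decides the sub-study, section 9.7 may require the change to be made by protocol amendment. It should be fixed before any comparative late-loss data are seen.

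### The lesion-level non-inferiority test that decides the randomized sub-study adjusts for within-patient correlation only if it looks large, so its one-sided error can exceed 5%

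*Protocol*

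**What the plan says.** Section 9.4 of the protocol (analysis of in-stent late loss at 270 days) sets the unit of the test: "The hypothesis testing will be based on all target lesions in the intent-to-treat population". The test "will be one-tailed and performed at the 0.05 significance level", using an asymptotic non-inferiority statistic. Within-patient correlation is covered by a single sentence: "If the correlation between lesions within patients is large, then repeated measures analysis will be considered". If non-inferiority is shown and late loss is lower with XIENCE, a two-sided t-test for superiority at 5% may follow. The section also says: "In case the use of parametric tests is inappropriate due to the distribution assumptions violation, non-parametric tests will be considered". It then rests the success of the sub-study on this non-inferiority test.

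Other sections fix the patient as the randomized unit. Section 4.2 requires all target lesions of a patient to receive the assigned treatment. Section 9.2 plans a "One-tailed non-inferiority test" and concludes that "approximately 252 subjects in the XIENCE EECSS arm and 126 subjects in the CYPHER arm will be required", with no intraclass correlation or design effect.

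Patients with several lesions are expected. Section 4.3 stratifies on complex lesions, which include triple-vessel treatment and two lesions treated in one vessel. Section 8.2 has a separate follow-up table for multiple target lesions. Section 6.4.2 admits patients whose disease is "suitable to be optimally treated with a maximum of 4 planned study stents".

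**The concern.** Lesions in one patient share that patient's biology, operator and stent type, so their late-loss values are likely to be positively correlated. A lesion-level statistic without a patient term counts them as separate pieces of information. Its standard error is then too small and its upper confidence limit for the difference too low, which favours non-inferiority.

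The safeguard in section 9.4 is weak on three counts. It has no threshold, its trigger is read from the trial's own data, and it commits the analyst only to consider another method. A moderate correlation could leave the unadjusted test in place while still moving the error rate. The sub-study stands or falls on this one test, and the nominal 5% is the only error control on that conclusion.

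**Working it through.** **Step 1: reproduce the planned sample size.** Inputs from section 9.2: one-sided alpha 0.05, power 90%, SD 0.53 mm in both arms, margin 0.17 mm, true difference 0, allocation 2:1.

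Control n = (1.645 + 1.282)² × 0.53² × (1 + 1/2) / 0.17² = 124.9, so 125 control and 250 XIENCE. The protocol states 126 and 252, at which power is 90.2%. The figure is reproduced. It rests on one independent observation per subject.

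**Step 2: error of a lesion-level test that ignores clustering.** With m lesions per patient, all in the same arm, and intraclass correlation ρ:

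- Design effect: DE = 1 + (Σm²/Σm − 1) × ρ
- Actual one-sided error: 1 − Φ(1.645/√DE)
- Actual two-sided error of the superiority t-test: 2 × [1 − Φ(1.960/√DE)]

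The protocol gives neither the distribution of m nor ρ. Both are assumptions, shown as a range.

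| Assumed share of patients with 1/2/3/4 lesions | Mean m | Σm²/Σm | ρ | DE | One-sided error |
|---|---|---|---|---|---|
| 90/10/0/0% | 1.10 | 1.182 | 0.1 | 1.018 | 5.2% |
| 90/10/0/0% | 1.10 | 1.182 | 0.5 | 1.091 | 5.8% |
| 82/16/2/0% | 1.20 | 1.367 | 0.3 | 1.110 | 5.9% |
| 82/16/2/0% | 1.20 | 1.367 | 0.5 | 1.183 | 6.5% |
| 60/30/10/0% | 1.50 | 1.800 | 0.1 | 1.080 | 5.7% |
| 60/30/10/0% | 1.50 | 1.800 | 0.3 | 1.240 | 7.0% |
| 60/30/10/0% | 1.50 | 1.800 | 0.5 | 1.400 | 8.2% |
| 65/25/7/3% | 1.48 | 1.865 | 0.5 | 1.432 | 8.5% |

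Worked example (last row): mean m = 0.65 + 0.50 + 0.21 + 0.12 = 1.48 and mean m² = 0.65 + 1.00 + 0.63 + 0.48 = 2.76. The ratio is 1.865, so DE = 1 + 0.865 × 0.5 = 1.432 and √DE = 1.197. Then 1.645/1.197 = 1.374, and the upper tail is 8.5%.

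Across the same range the two-sided superiority error is about 5.2% to 10% instead of 5%. Superiority is tested only when late loss is lower with XIENCE, so roughly half of that is a false claim in its favour.

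**Step 3: simulation.** True difference at the 0.17 mm margin, 252 and 126 patients, 20,000 runs per setting. The unadjusted test rejected in:

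- 5.7%, 6.0% and 6.5% of runs at mean 1.2 lesions and ρ of 0.2, 0.3 and 0.5
- 6.4%, 7.3% and 8.3% of runs at mean 1.5 lesions and the same ρ

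A patient-clustered variance gave 5.0% to 5.2% in every setting.

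**Step 4: power after adjustment.** Power = Φ(0.17/SE − 1.645), with SE = 0.53 × √[DE × (1/(126 × mean m) + 1/(252 × mean m))] and 0.53 mm read as the lesion-level SD. Over 1.1 to 1.5 lesions and ρ of 0.1 to 0.5 it is about 90% to 97%.

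**The case against.** The strongest reply is that the protocol never calls lesions independent. It names the correlation and a suitable remedy. The excess error needs positive correlation, enough multi-lesion patients, and a remedy left unused. A correlation of 0.5 is where an analyst would most readily call it large and adjust, so the top figures assume the safeguard fails where it is most likely to work. At the mild end the excess is about 0.2 percentage points. All of this stands, and the size is therefore given as a conditional range.

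The stent cap in section 6.4.2 is also weak evidence on lesion numbers, because section 7.3.3.2 allows planned overlapping stents in one lesion. Sections 4.2, 4.3 and 8.2 do show that multi-lesion patients are expected, but not how many.

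A statistical analysis plan could define the threshold and the model, and their absence here is not the point. The point is that the protocol itself fixes a lesion-level default with a discretionary exception, and section 9.7 requires major statistical changes to go through a protocol amendment.

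A reader might also infer that switching to a non-parametric test necessarily abandons the 0.17 mm margin. The text does not support that. It names no method, and a rank test on data shifted by the margin, or the matching confidence limit, tests a location shift against it. That shift equals the mean difference only under a pure shift model, which is a reason to keep such an analysis supportive.

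**Conclusion.** The point holds in conditional form. Followed as written, section 9.4 allows an unadjusted lesion-level test to decide the sub-study, and no other section makes the adjustment unconditional. With any positive correlation and some multi-lesion patients, that test exceeds its nominal 5%. The excess is about 0.2 to 3.5 percentage points (5.2% to 8.5%) under the assumed lesion counts and correlations, and the upper part applies only if the conditional adjustment is not used. The further effect of choosing the analysis after seeing the correlation is not quantified.

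A reader might infer that the 5% level is certainly breached, or that the whole trial is affected. Neither follows. The first depends on quantities the protocol does not give. On the second, late loss is the main secondary endpoint of the sub-study, while the trial's primary endpoint is analysed descriptively.

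**What to change.** In section 9.4, delete the sentence that makes the adjustment depend on the observed correlation. Prespecify one patient-clustered analysis to be used whatever that correlation is, for example a linear mixed model for lesion-level late loss with treatment as a fixed effect and a random patient effect. Name a single method: a mixed model, estimating equations and cluster-robust errors can weight multi-lesion patients differently, so offering a choice would reopen the problem. Declare non-inferiority if the one-sided 95% upper limit for the mean difference (XIENCE minus CYPHER) lies below 0.17 mm. Use the same model for any superiority test. Label any non-parametric analysis supportive, so that the decisive test stays on the stated mean difference.

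The cost is one paragraph of text, standard software and a slightly wider confidence limit. No extra patients are needed: at the planned 252 and 126 subjects, power stays at about 90% or more over the assumed range.
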